### Control group

The patients in the control group do not receive any specific guidance on related symptoms except by completing the same questionnaire as the intervention group. The postoperative management of patients follows the current standard management in the hospital and after discharge. Following discharge, all the participants follow-up at the same time as the intervention group. At the same time, we encourage participants to actively seek medical help if necessary.

### Statistical analysis

The primary and secondary outcomes will be analyzed based on the protocol set. To be included in the analyses, a participant must provide MDASI-LC data from the baseline and at least two additional time points, QLQ-C30 data from the baseline, and at least one postoperative time point. All outcomes will also be analyzed based on full analysis set. The analysis will be carried out on the thoroughly collected data with the definition of statistical significance as *P* ≤ 0.05. Classification variables will be expressed in frequency or proportion and compared between groups with the *χ*^2^ test. Continuous variables will be represented by $$\overline{x}\pm s$$ or *M*(*P*_25_, *P*_75_) and compared between groups using Student’s test or Wilcoxon rank sum test. The changes in PROs in the intervention and control groups will be compared using the generalized mixed-effect model. Missing data will be processed by multiple interpolations. Subgroup analysis of patients undergoing postoperative chemotherapy. Sensitivity analysis is mainly to compare the data without missing data to the data set with multiple imputed data.

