## Methods

### Trial design

This multicenter, open-label, randomized, parallel-group, superiority trial will be conducted at four tertiary hospitals in two cities of Western China, including Tangdu Hospital, Daxing Hospital, the Affiliated Hospital of Shaanxi University of Traditional Chinese Medicine, and the Second Affiliated Hospital of Xi’an Medical College. The total number of lung cancer operations is approximately 5000 in these four hospitals yearly.

Participants who fulfill eligibility criteria will be randomly assigned with a 1:1 ratio to either a control group with current standard management or an intervention group with new management methods designed by the lung cancer specialist and psychological consultants from the four hospitals. This protocol abided by the standard protocol for clinical trials [29], and the flow chart of this trial is shown in Fig. 2.

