**Clinical characteristics**									
Surgical procedure, surgical approach, extent of surgery, stage, postoperative length of stay, postoperative chemotherapy									

Interventions are based on participants’ ePRO scores, and if there is a target symptom score ≥ 4, there will be corresponding treatment

The adherence to the intervention measures will be evaluated at every given time. If the participants fail to comply with the intervention measures as required more than two times, it will be considered a severe violation of the study protocol and removed from the trial. If the participants have serious complications after the operation and cannot complete the PRO questionnaire with poor compliance or deliberately miss the questionnaire filling or request to withdraw, they will be stopped from further collecting the relevant data.

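### In this open-label superiority trial, the analysis set named for the primary outcome is selected after randomisation, and nothing makes the full analysis set primary

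*Protocol article*

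**What the plan says.** Trial design declares the trial type: "This multicenter, open-label, randomized, parallel-group, superiority trial will be conducted at four tertiary hospitals". Randomization and blinding adds that patients and specialists cannot be blinded.

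Statistical analysis names the set for the main results: "The primary and secondary outcomes will be analyzed based on the protocol set". An entry condition follows: "a participant must provide MDASI-LC data from the baseline and at least two additional time points, QLQ-C30 data from the baseline", plus at least one postoperative QLQ-C30. The section then says: "All outcomes will also be analyzed based on full analysis set". It does not define either set further or rank the two results.

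The text below Table 1, in the Intervention period section, has two rules that act after randomisation. On adherence: "If the participants fail to comply with the intervention measures as required more than two times, it will be considered a severe violation", with the consequence given as "severe violation of the study protocol and removed from the trial". On patients with serious complications who cannot complete the questionnaire, poor compliance, deliberately missed questionnaires or a request to withdraw: "they will be stopped from further collecting the relevant data".

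The Control group section says that controls complete the same questionnaire but get no specific symptom guidance.

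**The concern.** In a superiority trial the main comparison should be between the groups as randomised. Here the set named first for the primary outcome is filtered by what patients do afterwards.

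The filter may also be tied to the outcome. A target symptom score of 4 or more counts as a threshold event, and the same score triggers the intervention. If failures to comply are counted per alert, a patient with few threshold events has little chance of exceeding two failures, while a patient with many has ample chance. Controls have no such measures to fail. Removing the more symptomatic intervention patients would lower that arm's mean with no treatment effect, and lack of blinding gives further room for differential dropout.

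One secondary outcome shows the difficulty plainly. The post-discharge follow-up rate would be analysed in a set that already requires returned questionnaires.

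At stake is whether the headline result answers the trial's question, namely whether offering PRO-based management reduces threshold events.

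**Working it through.** **1. The plan's own figure.** Inputs from Sample size calculation: difference 0.3 SD, two-sided α = 0.05, power 80%, independent t-test, 20% loss.

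- Normal approximation: n = 2(1.960 + 0.842)² / 0.3² = 174.4, rounded up to 175 per group.
- Exact t-test: 175.4, rounded up to 176. The plan's 176 reproduces.
- Inflation: 176 / 0.8 = 220 per group. This reproduces too.

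The point therefore concerns the analysis population and not the arithmetic.

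**2. Size of the bias in general.** Let a fraction f of one arm be excluded, with a mean g SD above that of the patients kept. The full-arm mean is (1 − f) × kept + f × excluded, so the kept mean lies f × g SD below it. With f = 0.20 and g = 0.75 (both assumed), the shift is 0.15 SD, half of 0.3 SD.

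**3. Effect on type I error, closed form.** Assume no true effect and 220 per arm. The intervention arm loses the top fraction f on a latent normal trait correlated ρ with the outcome; the control arm loses none. With c = z(1 − f):

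- shift = ρ φ(c) / (1 − f)
- retained variance v = 1 − ρ² [φ(c)/(1 − f)] [c + φ(c)/(1 − f)]
- SE = √( v / (220(1 − f)) + 1/220 )
- type I error = Φ(−1.96 + shift/SE) + Φ(−1.96 − shift/SE)

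Worked case, f = 0.20 and ρ = 0.5: φ(c)/(1 − f) = 0.280/0.8 = 0.350, so the shift is 0.175 SD. Then v = 1 − 0.25 × 0.350 × (0.842 + 0.350) = 0.896, SE = √(0.896/176 + 1/220) = 0.098, shift/SE = 1.78, and the type I error is 43%.

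| f (assumed) | ρ (assumed) | Shift, SD | Share of 0.3 SD | Type I error |
|---|---|---|---|---|
| 5% | 0.2 | 0.022 | 7% | 5.6% |
| 10% | 0.3 | 0.058 | 19% | 9.2% |
| 20% | 0.3 | 0.105 | 35% | 18.2% |
| 20% | 0.5 | 0.175 | 58% | 43% |

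**4. Simulating the removal rule.** Null simulations with 220 per arm, 15 postoperative forms, seven symptoms and a patient frailty dropped intervention patients with more than two non-compliances. All behavioural inputs are assumptions. The first three rows assume mean 1.7 events per form and SD of the patient mean 1.27. The last three come from a separate run with mean 1.6 and SD 1.36.

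| Assumed behaviour | Excluded | Shift, SD | Type I error |
|---|---|---|---|
| 10% non-compliance per alert | 9% | −0.06 | 10% |
| 15% per alert | 21% | −0.15 | 34% |
| 20% per alert | 34% | −0.27 | 73% |
| 5% per alert form | 1.6% | −0.01 | 4.7% |
| Failures counted at each visit, unrelated to symptoms | 18% | 0 | about 6% |
| More symptomatic patients comply better | 13.5% | +0.04 | not reported |

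The separate run reproduced the first two rows closely: 9% and 21% excluded, −0.07 and −0.16 SD, 11% and 36%. Negative values favour the intervention.

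**5. Power after the change.** t-test power at 0.3 SD is 0.801 with 176 per group and 0.881 if all 220 contribute, provided that non-adherence does not dilute the effect.

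**The case against.** The strongest reply is that the text is milder than it first looks.

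- *Naming and ranking.* A reader might infer that the plan states a per-protocol primary analysis with the full analysis set as a mere secondary check. It does not: the article says protocol set, leaves it undefined, and gives no order of precedence. A full-analysis-set result for every outcome is prespecified. This stands as a limit on the wording. The gap remains, because nothing makes the full analysis set primary or settles a disagreement.
- *Both arms.* A reader might infer that only the intervention arm loses patients. The minimum-data rule and the rule on complications, missed questionnaires and withdrawal apply to both arms. Only the sentence on intervention measures can act mainly on one arm, and it is a rule for removal from the trial, so linking it to set membership is an inference. This stands, and the one-arm calculations are illustrations.
- *Direction.* A reader might infer that the bias must favour the intervention. Adherence is assessed repeatedly, and if failures are unrelated to symptom burden the bias is about nil. If sicker patients comply better, it reverses. This stands.
- *The 20% loss figure.* It covers overall loss and withdrawal and does not support f = 20% for adherence exclusions. This stands.
- *Multiple imputation is planned.* It does not help here, because it does not restore patients who are left out of the set.

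**Conclusion.** The point holds in its limited form. On the most sensible reading, the primary and secondary outcomes rest on a set selected after randomisation, by questionnaire completion in both arms and, through the removal rule, by adherence to measures that only the intervention arm receives. On the mildest reading, the headline population is not fixed at all. Either is unsuitable for the main result of an open-label superiority trial.

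The size is unknown. Illustrations with one-arm exclusion run from about 0.02 SD with 5.6% type I error to about 0.15–0.175 SD with 34–43% when about 20% are excluded. The flatter scenarios show no material bias, and heavier exclusion would give more. These results rest on assumed exclusion fractions and an assumed link to the outcome, and the sign is open. The case for the change is the loss of protection by randomisation, not any one of these numbers.

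**What to change.** Three changes belong together.

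1. In Statistical analysis, make the full analysis set primary for the primary and secondary outcomes, defined as all randomised patients in their allocated arm regardless of adherence. Define the protocol set and keep it as supportive.
2. State that the minimum-data rule does not restrict the full analysis set, and that missing outcomes there are handled by the planned multiple imputation. As worded, the rule applies to the analyses generally and could remove the same patients from both sets.
3. Reconcile the two rules below Table 1 with this, so that non-adherence does not end the collection of outcome data from patients who have not withdrawn consent. This concerns data collection only; how such patients are managed clinically is for the sponsor to settle.

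Swapping the sets in one sentence, without items 2 and 3, would leave a full analysis set that could lack the same patients' data.

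The sample size stays at 176, inflated to 220 per group. The cost is a few sentences, a little more follow-up and imputation work, and a possibly smaller effect estimate.

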### Intervention period

The questionnaire and parameters that will be measured to assess symptoms and life quality at each visit point are shown in Table 1. The participants will answer the MDASI-LC (ePRO) questionnaire through a WeChat applet within 1 week before surgery, the first, third, fifth, and seventh days after surgery, and every week after discharge till the 12th week. Participants can fill in the ePRO questionnaire by scanning the two-dimensional code and logging into their personal account after receiving the reminder message to fill in the WeChat applet. Moreover, the paper version of QLQ-C30 filled by the same participants within 1–2 days before the operation, 4 weeks, and 12 weeks after the operation will be submitted to the clinicians when the review process is completed. When one or more target symptoms (pain, cough, fatigue, sleep disorder, shortness of breath, sadness, and distress) occur and the score reaches the preset intervention threshold (above moderate, score ≥ 4) [32], the participants in intervention group will receive the standardized treatment suggestions in WeChat applet. At the same time, the participating specialists (thoracic surgeons) will also receive early alerting messages on their mobile phones to inform them to contact the patient through WeChat or phone within 24 h to provide the patient with management advices base on ePRO score, including, if not at all, consultation, education, drug guidance, and evaluation on the necessity of the trip to emergence, clinic, or hospital. In addition to the target symptoms, if the participants have other novel symptoms or their ePRO exceeds the threshold, standard treatment suggestions designed by the lung cancer specialist will emerge on the WeChat ePRO interactive interface [33–38]. The psychiatrists focus on the psychological symptoms (sadness and distress) of all patients in the intervention group. If the score is between 4 and 6 points, guidance to manage the psychological symptom will be given to the patients by the general specialist, while if the score exceeds 6 points, the patients will receive a telephone consultation with the psychiatrists. The measure used for symptom relief in the intervention group will comply with the latest guidelines and follow SOP manuals in all centers. In addition, the participating patients are not informed of the threshold level. Specialist will not receive warning messages from the PRO data of control group patients and will not access the patient data in the control group. During the trial, each center will provide the participating patients with on-site monitoring visits, telephone monitoring, and online or on-site guidance on managing the symptoms. If the patients concern their symptoms, they will decide whether to seek medical help based on their self-evaluation of their symptoms. The participating patients will be educated on how to seek medical help for severe symptoms through usual channels. All participants will be provided free long-term medical consultation via WeChat, which may promote participation and compliance.

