## Results and measurements

### Primary outcomes

The main PRO tools in this study include MDASI-LC and EORTC QLQ-C30. MDASI-LC covers 16 lung cancer- and treatment-related symptoms as well as six disturbances to everyday life caused by symptoms and can be completed in five minutes. All items were scored on a scale of 0–10, with 0 as “no symptoms” or “no impact on life” and 10 as “the most serious level” or “complete impact on life.” Besides, the patients can have 24 h as the recall period before filling in MDASI-LC. Comparably, EORTC QLQ-C30 lays out 30 items, incorporating five functional dimensions, three symptom dimensions, six single symptom dimensions, and two total health status items. These can be done in 5 to 8 min with a recall period of 1 week. EORTC QLQ-C30 scores items 1–27 by the range of 1–4 points, with 1 as “no symptoms” or “no impact on life” and 4 as “the most serious level” or “complete impact on life.” Additionally, items 28 and 29 focus on health status assessment and can be scored by 1 to 7, with 1 as very poor and 7 as very good. For the evaluation, the severity of symptoms and function deterioration increases along the increments of the scores. Conversely, the higher the health score, the better the quality of life. Both scales have been widely used in China’s clinical setting with good reliability and validity [39, 40]. The main measurement indicators and follow-up schedule are shown in Table 1. The primary outcome of this study is the mean number of target symptom threshold events with discharge 12 weeks, which include pain, cough, fatigue, sleep disorders, shortness of breath, sadness and distress. According to published literature, patients with a symptom score of 4–6 can be classified as moderate and ≥ 7 as severe [33]. Thus, we presented the score of 4 as the threshold for intervention and the targeted symptom score of ≥ 4 as a threshold event in this trial. A score of 1 can be given if one of the target symptoms is recorded to be ≥ 4 in one follow-up and 3 if three target symptoms are graded as ≥ 4.

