### Secondary outcomes

The secondary outcomes of this study include the changes in PROs (symptom severity, daily function, and quality of life) and follow-up rates after discharge. The trajectory for PROs is defined as the average score of symptom severity for seven targeted symptoms and the average score of six MDASI-LC daily functional intervention items from baseline to 12 weeks after discharge. The trajectory for quality of life comes from the quality of life scale (EORTC QLQ-C30), including the measurement results at baseline and the 4th and 12th weeks after discharge.

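### The lead analysis of the MDASI-LC primary outcome admits only patients who also supplied a baseline and a post-operative paper QLQ-C30, which feeds only a secondary outcome

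*Protocol article*

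**What the plan says.** All references are to the protocol article.

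- **Analysis set (Statistical analysis):** "The primary and secondary outcomes will be analyzed based on the protocol set".
- **Entry rule (next sentence):** the condition for entry reads "a participant must provide MDASI-LC data from the baseline and at least two additional time points, QLQ-C30 data from the baseline". The QLQ-C30 part in full is "QLQ-C30 data from the baseline, and at least one postoperative time point". Nothing limits the QLQ-C30 part to the QLQ-C30 analyses.
- **Second set and missing data (same section):** "All outcomes will also be analyzed based on full analysis set", with no separate entry rule given, and "Missing data will be processed by multiple interpolations".
- **Primary outcome (Primary outcomes):** "The primary outcome of this study is the mean number of target symptom threshold events with discharge 12 weeks". An event is one of seven target symptoms scored 4 or more, and no QLQ-C30 item enters the count.
- **Role of QLQ-C30 (Secondary outcomes):** it supplies the quality-of-life trajectory, a secondary outcome.
- **Mode and timing (Intervention period):** "the paper version of QLQ-C30 filled by the same participants within 1–2 days before the operation, 4 weeks, and 12 weeks after the operation". Table 1 ticks it at V2 (baseline), V10 (day 29) and V18 (day 86). MDASI-LC is electronic and is due at every post-operative visit.

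**The concern.** A missing secondary form decides who counts in the primary comparison. The two instruments differ in mode and schedule, so they can go missing separately. MDASI-LC comes through the applet, with electronic reminders and a personal call after discharge if it is not filled in that day. QLQ-C30 is a paper form handed to clinicians on two occasions after surgery.

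The two QLQ-C30 conditions do different harm. The baseline form is due before surgery, so requiring it mainly wastes data. Requiring a post-operative form selects on something that happens after randomisation, and there are three reasons to doubt that this selection is neutral:

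- Data collection stops for patients with serious complications who cannot complete the questionnaire (text following Table 1), so early drop-out can be tied to symptom burden.
- The trial is open-label, and only the intervention arm receives alert-triggered specialist contact within 24 hours.
- Follow-up rate is itself a secondary outcome, so the plan allows that the intervention may change retention.

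At stake are an avoidable risk of selection bias in the lead primary result and an avoidable loss of primary data.

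**Working it through.** **1. Who is excluded.** Before V10, Table 1 schedules post-operative MDASI-LC at V3, V4, V5, V7, V8 and V9 (days 1, 3, 5, 7, 14 and 22), which is six forms. V10 to V18 add nine, so there are 15 in all. The MDASI-LC part of the rule needs a baseline and two of these. Two kinds of patient meet it and still fail entry:

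- (a) patients lost before day 29, with up to six post-operative MDASI-LC forms;
- (b) patients who continue with MDASI-LC but have no baseline QLQ-C30, or neither later paper form.

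The Secondary outcomes section times the later QLQ-C30 forms from discharge, not from surgery. On that reading, the first one falls later still.

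**2. The plan's own sample size.** Inputs (Sample size calculation): difference 0.3 SD, two-sided α = 0.05, power 0.80, 20% loss.

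- Normal approximation: n = 2(1.960 + 0.842)² / 0.3² = 174.4, so 175 per group.
- Two-sample t-test: 175.4, so 176 per group, with power 80.1% at 176.
- Inflation: 176 / 0.8 = 220 per group.

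The stated 176 and 220 both reproduce.

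**3. Power if the QLQ-C30 condition removes more.** Group (a) is loss to follow-up or withdrawal and falls largely within the 20% allowance. Only group (b) is additional. The article gives no figure for it, so the extra fraction x is assumed. Evaluable n per group is 220 × 0.8 × (1 − x). The number to randomise to keep 176 is 220 / (1 − x), rounded up.

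| Assumed x | n per group | t-test power at 0.3 SD | Randomised per group to keep 176 |
|---|---|---|---|
| 0% | 176.0 | 80.1% | 220 |
| 2% | 172.5 | 79.3% | 225 |
| 5% | 167.2 | 78.1% | 232 |
| 10% | 158.4 | 75.9% | 245 |

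**4. Bias, as an illustration only.** If a fraction f of one arm is excluded and those patients average d SD more burden than the patients retained in that arm, the arm mean shifts by f × d. With assumed f = 10% in one arm, none in the other, and d = 0.5, the shift is 0.10 × 0.5 = 0.05 SD, which is one sixth of the 0.3 SD target. With equal exclusion and equal d in both arms, the shifts cancel.

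**The case against.** The strongest reply is that the full analysis set covers this. The paragraph gives the protocol set, then the entry rule, then the full analysis set as a further analysis. A reader might infer from the general wording that the rule governs the full analysis set too. The order of the sentences points the other way: a second set bound by the same rule would serve no purpose. So these patients are not shown to be lost to every analysis. What remains is that the protocol set leads, and the full analysis set comes second with no entry rule stated.

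Other points against, and how far they stand:

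- **Imputation.** A reader might infer that the rule removes the very patients for whom imputation is planned. It does not. A patient with two of 15 post-operative MDASI-LC forms is admitted, leaving up to 13 to impute, and one of the two later QLQ-C30 forms may also be missing. Only some patients with missing data are removed.
- **Early losses.** Counting everyone lost before the day-29 form as a cost on top of the 20% would count them twice. Such patients also hold little primary data. The outcome concerns the 12 weeks after discharge; if discharge is around day 7 (assumed), they have about two of the eleven weekly forms V8 to V18.
- **Few patients in group (b).** The baseline QLQ-C30 is filled in alongside MDASI-LC before surgery, and one of two later forms is enough. The extra loss may well be small.
- **Differential return.** The QLQ-C30 schedule and the reminders are common to both arms. A difference by arm is possible but is not shown.
- **Intent.** The rule may have been meant instrument by instrument. The text does not say so, and the choice changes who enters the lead primary analysis.

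**Conclusion.** The point holds for the lead, protocol-set analysis. As written, a patient with sufficient MDASI-LC data is excluded from an MDASI-LC-only primary outcome for want of a form that feeds a secondary one. This is a stated rule that works badly if followed, not a detail left to a fuller document.

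The likely cost in power is modest: from 80.1% to between 79.3% and 75.9% for an assumed extra exclusion of 2% to 10%, and nothing if no one falls in group (b). The main concern is selection on a post-randomisation event in an open-label trial. Its direction and size cannot be derived from the article.

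The conclusion does not extend to the MDASI-LC requirement of two further time points. A reader might want that removed as well, but nothing here shows it to be wrong.

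**What to change.** Split the entry rule by instrument before the data are analysed:

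- The MDASI-LC condition applies only to the MDASI-LC analyses, including the primary outcome.
- The QLQ-C30 condition applies only to the QLQ-C30 analyses.
- The full analysis set carries no QLQ-C30 condition for MDASI-LC outcomes and uses the planned multiple imputation.

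This takes a few sentences and needs no new data or change of sample size. The downside is slightly different numbers of patients across outcomes, which should be reported, and a little more imputation.

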**Methods and analysis:**

This multicenter, open-label, randomized, parallel superiority trial will be conducted at four hospitals in China. A total of 440 lung cancer patients will be recruited in this study, who will be randomly assigned to the intervention group or the control group in a ratio of 1:1. Any of the target symptoms reaches the preset threshold (score ≥ 4), the patients will accept the symptom management advices based on the PRO. The patients in the control group will follow the current standard procedure of symptom management. The symptom management system is an electronic management system based on WeChat mini programs. All patients will be evaluated for symptoms through the lung cancer module of the MDASI lung cancer-specific scale on the day before surgery, days 1, 3, 5, and 7 after surgery, and once a week during the 12-week post-discharge period. Simultaneously, the EORTC QLQ-C30 scale will be used to evaluate patients’ quality of life at baseline and the fourth and twelfth week after the surgery. The mean number of symptom threshold events of the intervention and the control groups were compared by *t*-test, and the changes of PRO were compared by a mixed effect model. The primary endpoint has been set as the 12-week post-discharge period.

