### Randomization and blinding

The stratified block randomization method will be used for this trial. The third-party statisticians will use the statistical software SAS9.4 PROC PLAN to generate random numbers and randomize the participating patients. Participants will be stratified by research center, and the appropriate segment lengths will be selected. Allocation of participants will be concealed using envelopes with consecutive numbers. The randomized numbers will be segmented, retained, and managed by the third party who will not be involved in the data collection. Each center assigned its participants according to the estimated number of participants and the enrollment sequence of each participant in that center. The random grouping table is pre-implanted into the WeChat applet. It will then be allocated to the intervention group or control group with a 1:1 ratio. Due to the nature of the intervention, the participating patients, specialist cannot be blinded. In order to reduce measurement bias, all personnel who assist in data collection and data analysts (the third party) will be blinded. As a result, unblinding will not occur in this trial.

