### Sample size calculation

The primary endpoint of this study was the mean number of symptom threshold events, which is calculated by averaging the number of target symptom threshold events per patient at each time point. The minimum important difference (MID) has been defined as the smallest difference in the scores of the PRO measure that patients perceive as beneficial or harmful and would lead the clinician to consider a change in treatment. The literature recommended that the minimum difference between the two groups should be ≥ 0.3 sd based on the clinical treatment comparison efficacy measured by PRO instruments [31]. To meet the MID (0.3 sd) with the PRO instrument for mean symptom threshold events, the sample size required for each group was 176 when rejecting the null hypothesis (difference between the two groups < 0.3 SD). A total of 352 samples are required in this study. According to the previous pre-investigation experience, the loss rate of follow-up and withdrawal was 20%; 220 patients should be the adequate number of participating patients for each group (176/0.8). Because this trial is an intervention study, the follow-up time is 3 months after major lung operations. The sample size calculation is based on the independent sample Student’s *t*-test, using a two-tailed test (*α* = 0.05, 1 − *β* = 0.8).

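### The primary comparison is an unadjusted test that uses neither centre nor baseline MDASI-LC, and the analysis section does not say which of two tests is primary: an efficiency loss, not a validity fault

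*Protocol article*

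**What the plan says.** The protocol article describes the primary comparison in three places.

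- **Abstract, Methods and analysis:** "The mean number of symptom threshold events of the intervention and the control groups were compared by *t*-test".
- **Sample size calculation:** the endpoint is a mean ("The primary endpoint of this study was the mean number of symptom threshold events"), the target effect is in SD units ("the minimum difference between the two groups should be ≥ 0.3 sd"), and the test is the two-sided independent-sample t-test ("The sample size calculation is based on the independent sample Student’s" t-test).
- **Statistical analysis:** a general sentence covers all continuous variables, which are "compared between groups using Student’s test or Wilcoxon rank sum test". It is paired with mean and SD, or median and quartiles, as the summary. It does not mention the primary endpoint and gives no rule for choosing between the tests.

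Two other statements bear on the point. Under Randomization and blinding, "Participants will be stratified by research center", and there are four centres. Under Statistical analysis, a participant enters the analyses only with a baseline MDASI-LC and at least two later ones. The only model named, a generalized mixed-effect model, is assigned to changes in PROs, which the Secondary outcomes section lists as secondary.

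**The concern.** A t-test or rank-sum test, as named, has no place for a covariate. The trial will hold two variables that could sharpen the primary comparison: the centre within which patients were randomised, and a pre-operative score on the instrument that defines the outcome. Leaving both out gives up precision that costs nothing to obtain.

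The second issue is consistency. The section that governs the analysis does not repeat the choice of t-test made elsewhere, and it admits a rank test that does not compare means. Endpoint and effect size are both defined on means. A switch to Wilcoxon would therefore change what is estimated, and the summary reported with it. The article also plans multiple imputation. A regression coefficient pools directly across imputed data sets; a rank-sum test does not.

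**Working it through.** **Inputs from the article:** difference 0.3 SD, two-sided alpha 0.05, power 0.80, 1:1 allocation, 176 per group before and 220 after 20% loss (Sample size calculation); four centres as strata. **Assumed, because the article gives neither:** r, the correlation of the baseline measure with the outcome, and c, the share of outcome variance between centres.

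**1. The plan's own figure.** The normal approximation gives n = 2(1.960 + 0.842)²/0.3² = 174.4, so 175. The exact noncentral-t solution is 175.4, so 176. Then 176/0.8 = 220. Both stated figures reproduce. Power at 176 per group is 80.1% (t) or 80.4% (normal).

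**2. Baseline adjustment.** The residual SD becomes √(1 − r²), so power = Φ(0.3·√(176/2)/√(1 − r²) − 1.960), with 0.3·√88 = 2.814. The equivalent gain in sample size is 1/(1 − r²) − 1.

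| r (assumed) | Power at 176 per arm, normal | Power, noncentral t | n per arm for 80% (normal) | Equivalent gain in n |
|---|---|---|---|---|
| 0 | 80.4% | 80.1% | 175 | 0% |
| 0.2 | 81.9% | 81.7% | 168 | 4% |
| 0.3 | 83.9% | 83.7% | 159 | 10% |
| 0.4 | 86.7% | 86.5% | 147 | 19% |
| 0.5 | 90.1% | 90.0% | 131 | 33% |

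**3. Centre adjustment alone.** Allocation is balanced within centre, so the true variance of the difference uses 1 − c, while the unadjusted test estimates it from the total variance. Hence:
- true alpha = 2[1 − Φ(1.960/√(1 − c))]
- unadjusted power = Φ((2.814 − 1.960)/√(1 − c))
- adjusted power = Φ(2.814/√(1 − c) − 1.960)

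| c (assumed) | True alpha, unadjusted | Power, unadjusted | Power, adjusted |
|---|---|---|---|
| 1% | 0.049 | 80.5% | 80.7% |
| 5% | 0.044 | 81.0% | 82.3% |
| 10% | 0.039 | 81.6% | 84.3% |

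**4. Upper bound on the effect of free test choice.** 20,000 null trials with 176 per group were simulated for each distribution. Both tests were run, and a trial counted as positive if either gave P ≤ 0.05.

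| Outcome distribution (assumed) | t-test alone | Wilcoxon alone | Either |
|---|---|---|---|
| Normal | 5.0% | 5.0% | 6.1% |
| Negative binomial, mean 1, size 1 | 5.0% | 5.1% | 7.2% |
| Negative binomial, mean 10, size 1 | 5.1% | 5.2% | 7.5% |
| Negative binomial, mean 10, size 0.5 | 5.2% | 5.0% | 7.9% |

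**The case against.** The strongest defence is that nothing is broken. The Abstract names the t-test for this endpoint and the sample size uses the same test. The Statistical analysis sentence is generic and, by pairing test with summary, reads as a choice by distribution rather than by P value. An unadjusted comparison after randomisation is unbiased and has the planned power. The gain from adjustment rests on an unknown r. The baseline is pre-operative while the outcome is post-operative symptoms over about 12 weeks, so r may be low; at 0.2 the gain is under 2 points. Most of this stands, and it limits the point to efficiency and wording.

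A reader might go further in four ways that the article does not support.

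- **That the primary test is open to choice after the results are seen.** Two of the three places point to the t-test. The 6–8% error rate arises only if both tests are run and the better result is taken, which the article does not describe.
- **That chance imbalance in pre-operative symptoms biases the result.** Such imbalance is random error, which the standard error already covers.
- **That ignoring centre inflates false positives.** It does the opposite.
- **That the earlier trial's 0 versus 2 threshold events (Background) makes a switch to Wilcoxon likely.** That trial covered one month and physiological symptoms only, and the article does not say whether the figures are means or medians. Here the outcome is averaged over many visits and covers seven symptoms.

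What remains is that no named primary test uses centre or baseline, and that the analysis section does not tie the primary endpoint to one test.

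**Conclusion.** The point holds as a worthwhile improvement, not as a fault in validity. The unadjusted t-test is correctly sized and keeps its 80% power. What is forgone through baseline is about 1.6 points of power at r = 0.2, 6 at 0.4 and 10 at 0.5: negligible at the low end and material from about 0.4. Centre adds 0.3 to 2.7 points for c of 1–10%. Both ranges rest on assumed values and on a large-sample approximation to ANCOVA. The direction is secure; the size is not known. The missing link between the primary endpoint and one test is a matter of wording. The covariates of the secondary mixed models are detail commonly left to an analysis plan and are not part of this point.

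**What to change.** In Statistical analysis, name one primary analysis that keeps the difference in means used in the Abstract and the sample size. This would be a linear regression (ANCOVA) of the per-patient mean number of threshold events on arm, centre and a baseline MDASI-LC target-symptom measure, with robust standard errors, reporting the adjusted mean difference and 95% CI. The baseline measure could be the number of target symptoms scoring 4 or more, or their mean severity. Mean severity keeps information that the count discards; either should be fixed in advance. Keep the unadjusted t-test and Wilcoxon test as sensitivity analyses only.

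The sample size stands and all variables are already collected, so the only cost is a documented analysis amendment. Trial status anticipated the last visit on 30 June 2023, so timing matters: make the change before outcomes are compared by arm, or label the adjusted analysis as added later.
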